### 2.5 Statistical analysis

The sample-size calculation is established based on a previous study (Formenti et al., 2019) on the primary outcome (incongruent condition of the Flanker task) using G^*^Power software. From a priori power analysis, observing a sample size of up to 84 individuals (β = 0.9) is requested, respecting a large effect size (Cohen's f equal to 0.4) with a type I error rate of α = 0.05. All data will be presented as mean ± standard deviation. The dataset will be tested for normal distribution using Shapiro–Wilk's normality test. Based on the study's design, the primary independent endpoints are the treatment groups and time. A two-way (treatment × time) repeated measures ANOVA will be used on each outcome variable to determine the interaction between the three time points (baseline, 8 weeks, 16 weeks) and groups (VT, VTD, C). If an interaction exists, the simple effect and pairwise comparisons will detect differences between groups at each time point. Subsequently an additional age stratification and comparison will be performed to check any age-related difference. If a main effect is detected, data will be analyzed using a *post-hoc* analysis (Bonferroni test). The significance level will be set at *p* < 0.05. Partial eta squared (Part 2) effect size will be used to estimate the magnitude of the difference within each group, respecting a threshold for small (0.01), moderate (0.06) and large effects (0.14) (Cohen, 2013).

If the Shapiro-Wilk's normality test is not passed, non-parametric tests will be applied. The Friedman Test will be performed to detect differences between groups over time in both primary and secondary outcomes. In addition, to examine where the differences occur, a Wilcoxon Signed Rank test with Bonferroni adjustment will be used as a *post-hoc* analysis. Also, in these tests, the significance level will be set at *p* < 0.05.

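### Plain Bonferroni is valid for the post-hoc tests, but with three levels per factor a step-down test at the same 5% family error never rejects less and can gain up to about 16 points of power on intermediate group contrasts

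*Protocol article*

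**What the plan says.** Section 2.5 (Statistical analysis) of the protocol article plans a two-way repeated-measures ANOVA on "the three time points (baseline, 8 weeks, 16 weeks) and groups (VT, VTD, C"). It describes three kinds of follow-up:

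- After a main effect: "If a main effect is detected, data will be analyzed using a *post-hoc* analysis (Bonferroni test").
- After an interaction: "If an interaction exists, the simple effect and pairwise comparisons will detect differences between groups at each time point". This sentence names no adjustment.
- If normality fails, a Friedman test, then "a Wilcoxon Signed Rank test with Bonferroni adjustment will be used as a *post-hoc* analysis".

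Bonferroni is the only multiplicity adjustment in the section. Significance is set at p < 0.05 and partial eta squared is the effect size; confidence intervals for pairwise differences are not mentioned. The sample size of 84 (28 per arm, section 2.2) is justified by "respecting a large effect size (Cohen's f equal to 0.4") and 90% power (printed as β = 0.9), "with a type I error rate of α = 0.05".

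**The concern.** A factor with three levels has three pairwise comparisons. Bonferroni holds each of them to 0.05/3 = 0.0167, even after one has already been rejected. With three means the null hypotheses are linked: if one pair truly differs, at most one of the other two equalities can be true, because two equalities would force the third. So once the smallest p-value has passed 0.0167, the remaining two can each be tested at 0.05 without the family error exceeding 5%. Bonferroni leaves that allowance unused.

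This matters because the study objectives (section 1.1) need more than one pair. They ask about training against control and also about loss of gains in VTD. The allowance Bonferroni leaves unused would mostly benefit the second and third pairs.

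**Working it through.** **Inputs from the article.** Three groups, three visits, 28 per arm, α = 0.05, f = 0.4, power 0.90, N = 84.

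**Assumed.** The article gives no pattern of means. Each pattern below is scaled to f = 0.4, where f is the SD of the three means divided by the within-group SD:

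- One group apart, (0, 1, 1): the SD of the means is √(2/9) = 0.471, so the scale is 0.4/0.471 = 0.85. C, VTD, VT = 0, 0.85, 0.85 SD.
- Equally spaced, (0, 0.5, 1): the SD is √(1/6) = 0.408, so the scale is 0.98. C, VTD, VT = 0, 0.49, 0.98 SD.
- In between, with VTD losing a quarter of the gain: 0, 0.71, 0.94 SD.

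**1. The plan's own figure.** One-way ANOVA with three groups and noncentrality λ = N·f² = 84 × 0.16 = 13.44. Power at N = 84 is 0.907; at N = 81 it is 0.895. So 84 is the smallest balanced total reaching 90%, and the stated figure reproduces.

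**2. Error control of the step-down test** (smallest p against 0.05/3, then the other two against 0.05):

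- All three equal: the first step is Bonferroni, so the error is at most 5%.
- Exactly one true equality: only one false rejection is possible, tested at 0.05 or less.
- All different: no false rejection is possible.

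Simulated family error behind the omnibus F test was 4.2% for Bonferroni, Holm and Shaffer when all means are equal. With one true equality it was 1.7% for Bonferroni, 3.4% to 5.0% for Holm and about 5% for Shaffer. In every simulated data set Holm and Shaffer rejected all that Bonferroni rejected.

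**3. Power** (28 per arm, one measurement per person, pooled variance on 81 df, pairs tested after a significant F; at least 200,000 simulated data sets per pattern):

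| Pattern and contrast | Bonferroni | Holm | Shaffer | Shaffer gain, points |
|---|---|---|---|---|
| One apart: each trained arm vs C | 76.5% | 79.6% | 83.5% | 7.0 |
| Quarter lost: VTD vs C | 58% | 64% | 72% | 14 |
| Quarter lost: VT vs VTD | 6% | 11% | 14% | 7 to 8 |
| Quarter lost: VT vs C | 85.5% | 86.6% | 88% | 2 to 3 |
| Equally spaced: VTD vs C, VT vs VTD (each) | 28% | 36% | 43% | 15.6 |
| Equally spaced: VT vs C | 88.4% | 88.8% | 89.2% | 0.8 |

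The chance of finding at least one true pair is the same for all three methods (88.7% one apart, 89.5% equally spaced), because the first step is identical.

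**4. Main effects in the repeated-measures setting** (f = 0.4 per visit, correlation ρ between visits assumed, no omnibus gate):

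- Group effect averaged over three visits, ρ from 0 to 0.9: Shaffer gains 0 to 18 points, depending on pair and pattern.
- Time effect, 84 people: the gain is at most 1.5 points at ρ of 0.5 or more, about 5 at ρ = 0.3 and about 11 at ρ = 0.

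**The case against.** The strongest reply is that Bonferroni is valid and familiar, and that nothing in section 2.5 is wrong or contradictory on this point. That stands: the plan has no type I error problem here. Nor is the extra power entirely free. It uses error allowance that Bonferroni leaves idle (1.7% against about 5% with one true equality), and step-down tests do not come with simple simultaneous confidence intervals. The second cost weighs little here, because the article plans no such intervals.

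Two further objections also stand and limit the point.

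- **Where Bonferroni applies.** A reader might infer that the trial's main comparisons lose 7 to 16 points. The text does not show this. The treatment hypotheses rest on the interaction and the group comparisons at each visit, and the sentence on those names no adjustment. If Bonferroni is not used there, they lose nothing to it.
- **Family size.** A reader might also take every post-hoc family to contain three pairs. Three groups compared at three visits give 3 × 3 = 9 pairs. Signed-rank tests between three visits within each of three arms also give 9. The article does not define these families, and the 0.05/3, 0.05, 0.05 rule does not apply to a family of nine.

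The equally spaced pattern is also harsher than the slight attenuation expected in sections 1.1 and 3. Even with the better method, its intermediate contrasts reach only 43% power.

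**Conclusion.** The point holds as a cheap gain in efficiency. For three pairwise comparisons of three means, plain Bonferroni is dominated at the same 5% family error by Holm with Shaffer's refinement. That follows from logic and needs no assumed effect.

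The size does need assumptions. The gain of about 7 points per true pair (one group apart) and of up to about 16 points on intermediate contrasts (equally spaced) holds for Shaffer's procedure on the group factor, with one measurement per person, f = 0.4 and 28 per arm. It is not a general loss across both factors or all pairs. It is under 1 point for the largest contrast when means are equally spaced, nil for finding at least one true pair, and small for time at moderate or high correlation. Holm alone yields about 0.4 to 8 points. No gain was calculated for the Wilcoxon branch. For VT, VTD and C at each visit the loss is conditional on Bonferroni being carried over to the interaction follow-up.

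**What to change.** Before any outcome data are seen, amend section 2.5 or the analysis plan as follows:

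- Replace the Bonferroni test by Holm's step-down. For any family of exactly three pairwise comparisons of three means, add Shaffer's refinement: the smallest p-value against 0.05/3 and, if that is significant, the other two against 0.05.
- For the signed-rank tests, now "a Wilcoxon Signed Rank test with Bonferroni adjustment", use Holm over however many tests the family contains. Holm needs no logical link between the hypotheses, so it remains valid if there are nine.

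The cost is a sentence or two of wording, with no new data or participants. No rejection that Bonferroni would have made is lost. The small downside is that matching simultaneous confidence intervals are less simple; if intervals are reported, show them unadjusted or at Bonferroni width and say which.

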### 1.1 Study objectives

The overall main purpose of this research project is to determine the effectiveness of perceptual-vision training on cognition and physical functioning in individuals with intellectual disabilities.

Specifically, the primary endpoint is to identify the role of eye training on cognitive performance in terms of inhibitory control. The secondary endpoints are to verify the contribution of vision training on postural control, upper and lower body strength and agility outcomes. The tertiary endpoint aims to verify any potential effect of age, reinforcing the concept of promoting healthy aging.

Our primary hypothesis is that perceptual vision training intervention will promote a greater increase in cognitive and motor performance compared to the usual care control group. In addition, the secondary hypothesis is that a period of detraining could slightly attenuate the training-induced gains achieved during the previous intervention period. The third hypothesis is to detect whether there is an age-related effect on the outcomes measured.

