### 2.2 Study design

This project is a three-arm, parallel, randomized controlled trial. In detail, Figure 1 highlights the flow diagram of the overall design setting. At the beginning, participants will have their body mass and height measured. After that, a 1-week familiarization period will be implemented during which participants will adapt to the exercise techniques used throughout the study. Following 1 week of baseline testing, participants will be randomly assigned to three groups: (i) a Visual Training Group (VT, *n* = 28) that will perform oculomotor exercises combined with postural control exercises (Formenti et al., 2019) for 16 weeks; (ii) a Visual Training-Detraining group (VTD, *n* = 28) that will follow the same training protocol of VT for the first 8 weeks, abstaining from any training for the following 8-weeks period (from week 9 to week 16) and (iii) a control group (C, *n* = 28) in which no intervention will be implemented. Randomization will be achieved using a random-number generator (https://www.random.org using a 1:1:1 ratio) and to ensure adequate allocation concealment this procedure will be carried out by a blinded external researcher. An independent researcher will conduct the allocation sequence until the interventions are assigned. A research team collaborator will enroll and assign participants to the three groups. Baseline testing will be repeated after 8 weeks (mid-training testing) and at the end of week 16 (post-training testing).

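### The only effect size named is a within-group partial eta squared, which does not measure benefit over control, and the main-effect post-hoc is not tied to the interaction

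*Protocol article*

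**What the plan says.** All of this is in the protocol article.

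- Section 1.1 states the primary hypothesis as a between-arm contrast: the intervention "will promote a greater increase in cognitive and motor performance compared to the usual care control group".
- Section 2.5 names the matching test. A two-way "repeated measures ANOVA will be used on each outcome variable to determine the interaction between the three time points" and the three groups. If the interaction is present, simple effects and pairwise comparisons between groups at each time point follow.
- Section 2.5 then adds a second route to post-hoc testing: "If a main effect is detected, data will be analyzed using a" Bonferroni post-hoc. It does not say which main effect is meant, or whether the interaction must be significant first.
- Section 2.5 closes the parametric plan with its only effect size, partial eta squared. That "effect size will be used to estimate the magnitude of the difference within each group", graded at 0.01 (small), 0.06 (moderate) and 0.14 (large).

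**The concern.** The effect-size sentence has two faults. First, it misdescribes the statistic. In a treatment × time ANOVA, partial eta squared belongs to a term (group, time or interaction) and is computed over all participants, so no value of it is a difference within each group. Second, if it is computed arm by arm to fit the sentence, it no longer addresses the hypothesis. The VT value would combine training with retest practice, regression to the mean and anything else that moves all arms. It has no sign and no unit such as milliseconds, seconds, errors or kilograms.

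The main-effect sentence adds to this. The time main effect is averaged over all arms, control included. The group main effect is averaged over all visits, including the baseline taken before randomisation. Neither one tests a greater increase than control.

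At stake is how the result will be read. A VT effect size labelled moderate or large, next to significant time post-hocs, is easily taken as the size of the training benefit even if control improved just as much.

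**Working it through.** **The plan's own figure first.** Inputs from sections 2.2 and 2.5: three arms "using a 1:1:1 ratio", 28 each; "observing a sample size of up to 84 individuals (β = 0.9) is requested" (0.9 is read as power); "respecting a large effect size (Cohen's f equal to 0.4"; and a test "with a type I error rate of α = 0.05". For a one-way three-group F test with λ = f²N:

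- N = 81: λ = 0.16 × 81 = 12.96, power 0.895.
- N = 84: λ = 0.16 × 84 = 13.44, power 0.907.

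So 84 is the smallest balanced N that reaches 0.90, and the figure reproduces. The planning effect is itself a between-group quantity: f = 0.4 gives η² = 0.16 / 1.16 = 0.138, which is almost the plan's threshold for large. The sample size is not affected by this point.

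**What a within-arm partial eta squared would show if training did nothing.** Assumptions, none of them in the document: every arm, control included, gains the same amount; unit SD; equal correlation ρ between visits.

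Within one arm of 28 at three visits, the time term has 2 df and the error 27 × 2 = 54 df. Partial η² = SS_time / (SS_time + SS_error). SS_time scales as a noncentral chi-square with λ = 28 × Σ(μ_t − μ̄)² / (1 − ρ). A close approximation to the mean is (2 + λ) / (56 + λ).

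- *No change.* λ = 0. The statistic is Beta(1, 27), with mean 1/28 = 0.036. That already exceeds the plan's threshold for small (0.01).
- *Gains 0.2 then 0.3 SD.* Mean 0.1667, Σ = 0.0278 + 0.0011 + 0.0178 = 0.0467. λ = 28 × 0.0467 / 0.5 = 2.61, or 28 × 0.0467 / 0.3 = 4.36. The approximation gives 4.61/58.61 = 0.079 and 6.36/60.36 = 0.105.
- *Half those gains (0.1 then 0.15 SD).* Σ = 0.0117, λ = 0.65 or 1.09. The approximation gives 0.047 and 0.054.

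**Time main effect in the full trial.** With N = 84, λ = 84 × Σ / (1 − ρ), on 2 and (84 − 3) × 2 = 162 df. For gains of 0.2/0.3 SD, λ = 7.84 or 13.07.

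| Equal gain in all arms (week 8 / week 16) | Mean partial η² within VT, ρ 0.5 / 0.7 | Time effect significant, ρ 0.5 / 0.7 |
|---|---|---|
| 0 / 0 | 0.036 / 0.036 | 5% / 5% |
| 0.1 / 0.15 SD | 0.047 / 0.054 | 22% / 34% |
| 0.2 / 0.3 SD | 0.077 / 0.103 | 70% / 90% |
| 0.25 / 0.5 SD | 0.140 / 0.198 | 99% / over 99% |

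The table uses the exact distributions. Simulation with 4,000 trials per setting agrees to within about one percentage point.

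**The interaction in the same settings.** A shared gain cancels out of it. It was significant in about 5% of simulated trials (5.1% and 5.4% at 0.2/0.3 SD). Its own partial eta squared, on 4 and 162 df, averages 2/83 = 0.024 whatever the shared gain.

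**Spread at 0.2/0.3 SD.** Within-VT partial eta squared exceeds 0.06 in about 54% to 69% of trials and 0.14 in about 15% to 27%. At half that gain the shares are about 28% to 35% and 5% to 6%.

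**The case against.** The strongest reply is that the inferential route is sound. Section 2.5 aims the ANOVA at the interaction and follows it with comparisons between groups, as section 1.1 requires. Bonferroni post-hocs after a main effect are routine in factorial ANOVA, and describing a time effect is not an efficacy claim. The simulated time effects are correct detections of a change that was put in, not false positives, and they depend on an assumed gain. Outcomes will also be shown as mean ± SD, so original units are not lost. Detailed effect-size definitions often sit in an analysis plan that is not shown.

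Most of this stands. A reader might infer that the trial swaps its randomised comparison for before-after statements, or that it will report a time effect as the training effect. The document supports neither: it tests the interaction and nowhere says that a main effect or within-arm change counts as efficacy. Nor is it safe to say that a null trial would usually show a moderate or large VT effect size, since at half the assumed gain most would not reach 0.06.

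What the reply does not remove is the stated text. The article does not leave the effect size for later: it fixes one, ties it to the wrong quantity and names none between arms. It also fixes a post-hoc trigger without a factor or a condition.

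**Conclusion.** The point holds as a fault in the effect measure and in one ambiguous sentence, not in the main test. The named effect size cannot quantify benefit over control. With no training effect it would average about 0.08 to 0.10 within VT at shared gains of 0.2/0.3 SD, about 0.05 at half that, and 0.036 with no change, while the interaction keeps its 5% level. These values rest on the assumed gains, a visit correlation of 0.5 to 0.7 and 28 completers per arm. That partial eta squared is not a within-group difference, and that no between-arm effect size is named, rests on no assumption. The main-effect sentence leaves open the reading of a shared time effect as benefit, and goes no further than that. It should be corrected before analysis.

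**What to change.** Change two sentences in section 2.5.

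1. Replace the within-group partial eta squared with the baseline-adjusted between-arm difference, VT versus C and VTD versus C, with 95% CI in the original units of each outcome. A standardised difference, or the partial eta squared of the interaction term, may be added.
2. State that only the interaction or the pre-specified between-arm contrast supports a claim of efficacy. Main-effect post-hocs, with the factor named, and within-arm changes are descriptive.

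The cost is wording and a little extra analysis. No new data are needed and the sample size does not change.

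### If normality fails, the named fallback tests (Friedman, then Wilcoxon signed-rank) do not compare the arms, so the primary hypothesis goes untested for that outcome

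*Protocol article*

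**What the plan says.** Section 1.1 states a between-arm hypothesis: vision training should produce a "greater increase in cognitive and motor performance compared to the usual care control group". Section 2.2 gives the design: "This project is a three-arm, parallel, randomized controlled trial", randomised "using a 1:1:1 ratio" with 28 people per arm. On timing it says: "Baseline testing will be repeated after 8 weeks (mid-training testing) and at the end of week 16 (post-training testing".

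Section 2.5 has two branches. The main one is a treatment-by-time repeated measures ANOVA, followed by pairwise comparisons of groups at each time point. The other applies if the Shapiro–Wilk "normality test is not passed, non-parametric tests will be applied". For it the article says: "The Friedman Test will be performed to detect differences between groups over time in both primary and secondary outcomes". To locate the differences, "a Wilcoxon Signed Rank test with Bonferroni adjustment will be used as a" post-hoc analysis. No rank test for independent groups is named anywhere in the article.

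**The concern.** The three arms are different people. Friedman's test and the signed-rank test are both for related samples: they compare measurements within the same person. The article gives Friedman a purpose, finding differences between groups, that it cannot serve in a parallel-group trial. This is a wrong statement about named tests, not a detail left to an analysis plan.

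Two things are at stake. First, for any outcome sent down this branch, the question the trial was set up to answer is not tested. If the gap is repaired after the data are seen, the between-arm test becomes post hoc. Second, the only results this branch yields are statements about change over time. The same tests are taken three times, so scores may improve through repetition alone. A reader who takes significant change in a trained arm as evidence of training has no protection from the control arm.

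**Working it through.** **1. The plan's own figure.** Section 2.5 bases the sample size "on the primary outcome (incongruent condition of the Flanker task) using G^*^Power software", with Cohen's f = 0.4, α = 0.05, power 0.9 (printed as β = 0.9) and N = 84. For a one-way, three-group F test the noncentrality is λ = N·f² = 84 × 0.16 = 13.44, on 2 and 81 degrees of freedom. This gives power 0.907, and 84 is the smallest multiple of three that reaches 0.90. Two repeated-measures variants (three measurements, assumed correlation 0.5) give other totals: 21 for the within-between interaction and 57 for the between factor. The stated N therefore reproduces as a comparison between arms, which the fallback lacks.

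**2. Does arm enter the Friedman statistic?** With n participants, k visits and R_j the sum over participants of the within-person ranks at visit j:

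Q = 12 / [n·k·(k+1)] × ΣR_j² − 3·n·(k+1)

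With n = 84 and k = 3 the multiplier is 12/1008 = 1/84 and the last term is 3 × 84 × 4 = 1008, so Q = ΣR_j²/84 − 1008. No term carries an arm label, so reallocating the labels at random leaves Q as it was. Adding a constant to all three values of a person does not change that person's ranks. Numerically, adding 10 to every value in one arm of 28 gave Q = 3.738, p = 0.154, both before and after. This needs no assumption about the data.

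Running Friedman separately in each arm does not help: it gives three within-arm p-values and no test of their difference. The signed-rank test needs pairs, and participants in different arms are not paired.

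**3. How plausible is the branch?** The outcomes are response times and percent correct (Section 2.4.2), and timed tests, balance errors and water spills (Section 2.4.3). Such data are often skewed, bounded or discrete. Section 2.5 does not say whether Shapiro–Wilk is applied to pooled data, arm-by-visit cells or residuals. For one cell of n = 28, by simulation under assumed distributions:

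- Lognormal times, log-SD 0.25 to 0.35: the test fails in about 25% to 45%.
- Accuracy around 90% over an assumed 50 trials: it fails in about 23% with plain binomial variation, rising to about 96% with strong overdispersion (intraclass correlation about 0.10).

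**4. What if within-arm significance is read as a training effect?** Simulation with 28 per arm, three visits, no training effect and the same practice gain in every arm. The documents give no practice gain or correlation, so both are assumed. Ranges cover correlations 0.5 to 0.7 and repeated runs.

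| Practice gain at week 8 / week 16 (SD) | VT significant, C not | Either training arm significant, C not |
|---|---|---|
| 0 / 0 | about 5% | about 8% to 9% |
| 0.1 / 0.15 | 7% to 10% | 13% to 19% |
| 0.2 / 0.3 | 16% to 22% | 29% to 37% |

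Kruskal–Wallis on the change from baseline to week 16 rejected in 4.5% to 4.9% of null trials (correlation 0.7, practice gains of 0 to 0.5 SD). An equal practice gain does not disturb a test that compares arms.

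**The case against.** The strongest reply is that the defect is conditional. The main analysis is a group-by-time ANOVA with comparisons between groups, and it does address the Section 1.1 hypothesis. This stands. A reader might infer that the trial never tests its hypothesis, or that the fallback will probably be the analysis used. The article supports neither. Failure rates of 37% for perfectly normal data (1 − 0.95⁹ = 0.37) and above 90% for lognormal times can be obtained, but only by testing nine arm-by-visit cells and switching if any one fails. The article states no such rule.

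A second reply concerns false positives. Under the 0.2 / 0.3 SD practice gain, Friedman pooled over all 84 participants is significant in about 53% to 80% of simulated trials, and it is tempting to call that the type I error. It is not: the test correctly detects a real change over time. It misleads only if read as a training effect, and the protocol does not state 'VT significant, C not' as a decision rule. The percentages above are therefore consequences of a possible misreading, under assumed practice gains.

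A third reply is that a full analysis plan could supply the missing test. That would excuse an omission. Here the article names the tests and gives them a purpose they cannot serve, so the reply does not remove the point.

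**Conclusion.** The point holds in conditional form. For any primary or secondary outcome that fails Shapiro–Wilk, the plan as written contains no comparison of VT, VTD and C, and the between-arm hypothesis is not tested. This follows from the construction of the two tests and rests on no assumed figure.

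The sizes do rest on assumptions. Single-cell failure of about 25% to 45% for response times and 23% to 96% for accuracy depends on the assumed spread. The rate of 'VT significant, C not', about 5% to 20% (about 8% to 36% for either training arm), depends on a practice gain of 0 to 0.3 SD, a correlation of 0.5 to 0.7, and a reader treating within-arm significance as a training effect.

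The finding does not show that the ANOVA is wrong. Replacing it, or dropping the normality check in favour of other models, would be a matter of preference. Because the faulty branch covers the primary outcome and is cheap to correct, it should be corrected before any outcome data are examined by arm.

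**What to change.** Replace the Friedman and signed-rank fallback in Section 2.5 with a rank-based procedure that compares arms. One option is Kruskal–Wallis on change from baseline at weeks 8 and 16, followed by Bonferroni-adjusted Mann–Whitney tests between arms. The text should state the set of comparisons over which Bonferroni is taken: three arm pairs at two visits make 3 × 2 = 6. Rank ANCOVA adjusting for baseline is an alternative. State also what Shapiro–Wilk is applied to, so that the choice of branch is fixed in advance. Friedman and signed-rank may stay only as descriptive within-arm analyses, labelled as such.

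The cost is one reworded paragraph and slightly more analysis code, with no added participants or visits.
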